### Recruitment

Two types of participants will be recruited for Phase II: patients and pharmacists. Patients (n=20) asked to participate will be Hispanic men and women aged 50 years and older with T2D who have been on diabetes medications for at least 90 days but who are not adherent (ie, <80% adherent) and have increased diabetes markers (ie, HbA_1c_ >7% and fasting glucose >125 mg/dL). In addition, they should be able to meaningfully participate in the informed consent process, demonstrate poor acculturation based on the Marin Acculturation Scale, be comfortable speaking Spanish (during the preconsent or consent process), have and use a smartphone or tablet, and be willing to participate in a single visit lasting approximately 90 minutes. Exclusion criteria will include cognitive or psychiatric difficulties so severe as to make the person unable to meaningfully participate in the informed consent process, diagnosis of Alzheimer disease or any other dementia, or receiving pharmacotherapy for Alzheimer disease, and severe retinopathy or visual impairment that impacts the ability to see module content on a smartphone or tablet. Pharmacist participants (n=10) asked to participate will be licensed pharmacists providing CMM to Hispanic patients with T2D in an ambulatory care setting. In addition, they should be able to meaningfully participate in the informed consent process and be willing to participate in a single visit lasting approximately 90 minutes.

Only patients will be recruited for Phase III. Patients asked to participate will be Hispanic men and women aged 50 years and older with T2D who have been on diabetes medications for at least 90 days but who are not adherent (ie, <80% adherent) and have increased diabetes markers (ie, HbA_1c_ >7% and fasting glucose >125 mg/dL). Inclusion criteria will be similar to those in Phase II. However, they must be willing to participate in a baseline office visit and 1‐2 subsequent follow-up office visits lasting 60‐90 minutes, with each visit spaced 3‐4 months apart. Exclusion criteria are similar to those described in Phase II.

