### Phase III

The third phase will test health outcomes: medication adherence, HbA_1c_, and fasting blood glucose. During this phase, the pharmacist will use the digital health app with 40 adult Hispanic patients with T2D who meet the inclusion requirements (stated under the ”Recruitment” section). The study will take place at the Athens Neighborhood Health Center. If by 6 months, we have not recruited at least 25 patients, we will pursue another local federally qualified health center. After consent, patients will be instructed on downloading the digital health app, completing the modules within the first 2 weeks, and generating the QR code. Their preference for either submitting the QR code via email or bringing it to their next appointment will be confirmed. Medication adherence will be measured using scales previously used by the investigators (the Gonzalez-Lu questionnaire and the visual analog scale) [49,50]. The Gonzalez-Lu questionnaire and visual analog scale are being used due to their ease of use and strong reliability and correlation to electronic measurements of medication adherence [51-53]. Baseline HbA_1c_ and blood glucose levels (fasting) will be measured via labs conducted as standard medical practice. A follow-up visit will occur 3‐4 months later. Depending on patients’ responses, an additional visit 3‐4 months later may be needed. The app would immediately assist a patient who is nonadherent due to not knowing how to take a medication (eg, the app would explain that taking metformin with food optimizes effectiveness and lowers side effects). However, a patient may be nonadherent due to the inability to pay for a particular medication; this would be captured by the app but not addressed immediately because they chose to provide their QR code at the follow-up appointment and not when the issue arose. In such a scenario, the patient would have a follow-up visit an additional 3‐4 months after appropriate changes are made (eg, selecting another medication). In summary, Phase III will test our Aim 2 hypothesis that the app will improve medication adherence (>80% average adherence for the individual), HbA_1c_ (≥0.75% reduction), and fasting glucose (≥25% reduction) from baseline. These reductions are reasonable target endpoints based on the literature [54-56].

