The primary endpoint of Aim 2 is to improve adherence and health outcomes. We completed power analyses for this aim using a mixed-effects simulation routine in Power Analysis Sample Size (PASS 16; NCSS, LLC) software, and drawing effect size estimates from the literature on the impact of pharmacist counseling on diabetes control [59,60]. This analysis shows our planned sample size of 40 will provide a power of 0.85 to detect a significant change from baseline in outcome measures. Outcome measures include improvements in adherence and a reduction in HbA_1c_ and fasting glucose. We will evaluate differences before and after the intervention (eg, 3‐8 months later) using repeated-measures mixed-effects models, enabling us to evaluate not only the significance of change but also the impact of key covariates (age, gender, and health literacy) and effect size for use in planning a larger trial.

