### Limitations

While several strengths have been discussed, the study is not without limitations. Limitations include a small sample size, and the current plan is to conduct the study at a single location. Therefore, the generalizability to other populations may remain unclear. In addition, there could be difficulties with technology among older adults (eg, aged ≥65 years); however, we will attempt to mitigate this risk by recruiting participants with T2D across the eligible older adult age range. In addition, there is no control group for the pilot study. Therefore, the significance of the results may be limited when assessing if the health outcomes are attributed specifically to the intervention or other confounding factors.

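### Phase III selects patients on the three measures it then tests for change in a single arm, and does not require a baseline separate from the qualifying value, so regression to the mean may count as app effect

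*Protocol article*

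**What the plan says.** The Recruitment section sets a 90-day minimum on diabetes medication and describes the Phase III patients as those "but who are not adherent (ie, <80% adherent) and have increased diabetes markers (ie, HbA_1c_ >7% and fasting glucose >125 mg/dL". The Phase III section then states: "The third phase will test health outcomes: medication adherence, HbA_1c_, and fasting blood glucose". The Abstract calls these the primary outcomes.

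The Aim 2 hypothesis is that the app will "improve medication adherence (>80% average adherence for the individual), HbA_1c_ (≥0.75% reduction), and fasting glucose (≥25% reduction) from baseline". Under Procedures, Aim 2, the power claim is that "our planned sample size of 40 will provide a power of 0.85 to detect a significant change from baseline in outcome measures". The comparison is before versus after, "using repeated-measures mixed-effects models, enabling us to evaluate not only the significance of change but also the impact of key covariates", and the resulting effect size is to be used in planning a larger trial.

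On the baseline, the Phase III section says that HbA1c and glucose "levels (fasting) will be measured via labs conducted as standard medical practice". The Measures section gives the clinic chart as the source of laboratory data. Procedures describes a screening interview by telephone or in person, and Recruitment mentions a baseline office visit. Nowhere is it said whether the values that qualified a patient may also be the analysed baseline.

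The Limitations section concedes that "there is no control group for the pilot study" and that attribution may be limited by other confounding factors. Regression to the mean is not named.

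**The concern.** A patient must be on the wrong side of three cut-offs at once to enter. Each measure varies within a person, so some patients qualify because a reading was worse than their usual level. If that reading is also the baseline, the next one will on average be better with no intervention. A test of change against zero then uses the wrong null value, and no control arm is there to subtract the drift.

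Three things are at stake:

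- the significance test for each outcome;
- the adherence target, since above 80% is the mirror image of the entry rule of below 80%;
- the effect size passed to the larger trial, which would be too large and would make that trial too small.

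**Working it through.** **1. The plan's own figure.** The power of 0.85 at n = 40 cannot be reproduced. The article gives no effect size, SD of change, alpha or sidedness, only that it is "drawing effect size estimates from the literature on the impact of pharmacist counseling on diabetes control". Solved backwards with a paired t test at two-sided 0.05, it implies a standardized change of 0.486. For a 0.75-point HbA1c change, that is an SD of change of 0.75 / 0.486 = 1.54. The 0.486 serves below as a yardstick; its absence from the article is not part of this point.

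**2. Inputs.** From the article: the three cut-offs, n = 40, change tested against zero, one arm. Assumed, because the article gives none of them:

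- retest correlation ρ: HbA1c 0.65–0.85, glucose 0.40–0.70, adherence 0.50–0.80;
- clinic means (SD): HbA1c 7.5–9% (1.5–1.8), glucose 145–190 mg/dL (45–60), adherence 65–80% (16–20);
- correlation of stable components: 0.6 between HbA1c and glucose, −0.2 between each and adherence.

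**3. Formula, with adherence worked by hand.** For a normal measure selected below a cut-off c, the expected change with no effect is (1 − ρ) × (μ − E[X | X < c]). Take μ = 75, SD = 18, ρ = 0.65.

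- z = (80 − 75) / 18 = 0.278, and φ(z)/Φ(z) = 0.630.
- Selected patients lie 18 × 0.630 = 11.3 points below the clinic mean.
- Expected gain = 0.35 × 11.3 = 4.0 points.
- Variance of the selected values = 324 × (1 − 0.278 × 0.630 − 0.630²) = 139.
- SD of change = √(0.35² × 139 + 324 × (1 − 0.65²)) = 14.3.
- Standardized change = 4.0 / 14.3 = 0.28. The noncentrality is 0.278 × √40 = 1.76.
- Chance that t exceeds 2.023 (39 df) = 0.40.

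With adherence bounded at 0–100 and all three cut-offs applied jointly, simulation gives a gain of 3.6 points and a chance of about 0.35.

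**4. All three measures, simulated with zero true change.** Qualifying value used as baseline, n = 40, two-sided 0.05, favourable results only (nominal 0.025):

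| Scenario (ρ for HbA1c / glucose / adherence; clinic means) | HbA1c fall; false improvement | Glucose fall; false improvement | Adherence gain; false improvement |
|---|---|---|---|
| 0.85 / 0.70 / 0.80; 9, 190, 65 | 0.05; 0.05 | 1.7%; 0.07 | 1.4; 0.11 |
| 0.75 / 0.55 / 0.65; 8, 160, 75 | 0.14; 0.12 | 3.8%; 0.15 | 3.6; 0.35 |
| 0.65 / 0.40 / 0.50; 7.5, 145, 80 | 0.25; 0.25 | 6.6%; 0.34 | 5.7; 0.69 |

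Across the grid the standardized drift is 0.05–0.21 (HbA1c), 0.08–0.25 (glucose) and 0.12–0.40 (adherence), against the yardstick of 0.486. At least one of the three is falsely significant in about 21–85% of studies. About 9–31% of patients exceed 80% adherence at follow-up with no effect.

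**5. Wider inputs.** Drift scales roughly with 1 − ρ. At ρ = 0.88 the lowest HbA1c fall becomes 0.05 × 0.12/0.15 = 0.04. At ρ = 0.80 the lowest glucose fall becomes 1.7 × 0.20/0.30 = 1.1%, with a false-improvement chance of about 0.06. For adherence, the formula in step 3 gives:

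- mean 65, SD 15, ρ = 0.8: gain 0.9 points, chance 0.08;
- mean 85, ρ = 0.6, SD 15–18: gain 6.1–7.1 points, chance 0.83–0.86.

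**6. Against the targets.** HbA1c: 0.04/0.75 = 5% to 0.25/0.75 = 33% of the target. Glucose: 1–7% against 25%.

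**7. Effect on the larger trial (illustration).** If an observed standardized HbA1c change of 0.486 contained the middle-scenario drift of 0.13, the remainder would be 0.356. Required size goes as 1/d², so it would be 0.486² / 0.356² = 1.9 times what the observed value suggests.

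**8. With a separate baseline.** If the baseline is measured afresh, with errors independent of the qualifying value, false improvement returns to 0.023–0.027 per measure and 0.071–0.076 for at least one of three.

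**The case against.** The strongest reply is that the text never says qualifying values are reused. It has a screening interview and then a baseline visit, it says baseline labs will be measured, and a telephone screen cannot draw blood. A condensed article may leave this detail to the full protocol. This stands: the bias is conditional on reuse. It does not close the point, because chart labs and a same-day adherence answer would satisfy the text as written. A measurement never taken also cannot be recovered by a later analysis plan.

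Second, the hypothesis asks for more than a non-zero change. This also stands for HbA1c and glucose, whose targets regression alone would not reach. It does not help adherence or the significance test.

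Third, this is a pilot, the missing control is disclosed, and a controlled study is to follow. That lowers the severity. But a general caveat on confounding does not address a drift that the entry rule itself creates and that can be reduced without a control arm.

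Fourth, the size depends heavily on the assumed clinic mean. The highest adherence rates need a source mean at or above the cut-off, and the Phase III section describes the adherence scales as strongly reliable. This is fair, and is why a wide range is given.

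**Conclusion.** The point holds conditionally and should be fixed before Phase III. If qualifying values serve as baseline, regression to the mean would be counted as app effect in all three outcomes. The direction follows from the design; the size does not, because every reliability and clinic distribution is assumed.

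Across plausible inputs, the drift is an HbA1c fall of about 0.04–0.25 points, a glucose fall of about 1–7% and an adherence gain of about 1–6 points (about 7 if the clinic mean is at or above 80%). The chance of a false significant improvement is then about 0.05–0.25, 0.06–0.34 and 0.08–0.7 (up to about 0.86 for adherence with clinic means of 80–85%), against 0.025.

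A reader might infer that the p-values are invalid as planned, or that regression alone could make the study succeed. The documents support neither. Reuse is permitted but not stated, and the HbA1c and glucose targets lie well beyond what regression would produce.

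**What to change.** - Determine eligibility from the screening-interview adherence answer and the latest chart labs before consent.
- Re-measure adherence at the baseline visit, on a separate day. Use the next standard-care labs, drawn before the app is used, as the analysed baseline, whether or not the values still meet the cut-offs.
- Keep qualifying values out of the change analysis.
- Report the screening-to-baseline change descriptively. It is an indication of regression to the mean, not a clean estimate, because chart labs vary in age and care may change in between.
- Name regression to the mean in the Limitations.

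The cost is one repeat of a short scale and abstraction of labs already on file. Some patients will have a baseline inside the target range, and the observed change will be smaller. The gain depends on independent errors, so a same-day repeat would achieve less. Secular trend and the effect of pharmacist care itself stay uncontrolled, and the existing caveat must still cover them.

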### Measures

Data to be collected include participants’ demographics (eg, age, gender, and country of origin), self-reported medication adherence (eg, Gonzalez-Lu questionnaire and visual analog scale), and laboratory values (eg, HbA_1c_ and fasting glucose) from the clinic chart. Most self-reported data will be collected on paper and transferred into electronic databases secured on university-issued password-protected computers. Data will only be linked to participants’ identities by way of an identification number, and no personally identifiable information other than the identification number will be included with the data. The correspondence between participant identification numbers and their identity will be kept separately. All other data will be kept on password-protected university computers. In addition, during Phase II, individual software testing sessions will be recorded, with computer screen recordings of participant behavior (patients and pharmacists), while notes are taken by the investigator. These recordings will also be kept on password-protected university computers and will only be associated with the identification number and not with any personally identifiable information. Any recordings on software (eg, Lookback Usability Testing software) are also password-protected and will not include any protected health information. Lookback Usability Testing software provides the ability to assess usability by recording the participants’ interaction with the digital intervention. During Phase III, the pharmacists who are providing care to patient participants will have the ability to decrypt the QR code and match the patient with the identifier. This will allow the pharmacist to place the electronic file into the patient’s protected folder in their electronic health records. These records are password-protected and housed on password-protected computers. Please note this is not any different than the standard of care and normal operating procedures when medical records are received from other sources and securely uploaded to the patient’s electronic record.

### Procedures

Before the recruitment process, University of Georgia Institutional Review Board (IRB) approval for the proposed human participants research protocols will be secured, as well as any review required by the Athens Neighborhood Health Center. The study will also be registered on the United States government clinical trials website.

Overall, potentially eligible patient participants (for Phase II and III) will be recruited from patients at the Athens Neighborhood Health Center during their regular appointments. In addition, bilingual flyers will be posted in the clinic’s waiting room. Patients will be able to contact the investigator or clinician via email or phone call in English or Spanish to obtain more information about the study and/or express their interest in the study. Once patient participants are identified, a telephone screening or face-to-face interview in Spanish will be conducted for each potential participant. During the screening interview, participants will be informed of the nature of the study and may participate if interested and if the eligibility criteria are met. If they choose not to participate, they will be thanked for their interest and reminded that not participating does not impact their standing with the clinic. Potential pharmacist participants for Phase II will be recruited from the clinic site and locally (in the state of Georgia), as well as from other states serving Hispanic populations. As a result, it is important to note that pharmacist participants may be remotely interviewed via a secure server (ie, Zoom Meetings software) during Phase II. While pharmacists will have the option for remote interviews, visits for patient participants will all be conducted in person (face-to-face).

#### Aim 1

The primary endpoint of Aim 1 is to have a digital app that is user-friendly to both the patient and pharmacist. Regardless of whether the interview is face-to-face (for patients) or virtual (for some pharmacists), the software used (Lookback and Atlas.ti [Lumivero]), along with the recorded interviews, will allow us to capture information needed to conduct a thorough analysis. For each group of 5 participants, qualitative data (interviews and screen recordings) will be coded to identify features of the intervention that benefited or hindered the system’s ease of use and participants’ user experiences. Analysis will be based on an existing coding framework designed for medical interventions and expanded based on usability standards [38,55,56]. Analyst triangulation will be conducted to ensure high intercoder agreement. Issues found to have negatively impacted user experiences will be resolved before testing with new groups of 5 participants (for both patients and pharmacists). In addition, the SUS, AEOUS, TAM, and time to complete will be analyzed using descriptive statistics to provide quantitative snapshots of system quality for each group. This process of qualitative and quantitative analysis may be repeated with groups of 5 participants until no further difficulties are identified and benchmark scores are achieved for the SUS, AEOUS, and TAM. In summary, phase II will iteratively refine the digital apps based on qualitative analyses and test our Aim 1 hypothesis that the apps will have above-average usability and acceptability (SUS: mean score: ≥71 and AEOUS: mean score ≥5) with an overall goal that the digital apps will be acceptable (via TAM) by ≥90% of the patient participants and ambulatory care clinical pharmacists. These measurable targets are based on published data [40,57,58].

#### Aim 2

The primary endpoint of Aim 2 is to improve adherence and health outcomes. We completed power analyses for this aim using a mixed-effects simulation routine in Power Analysis Sample Size (PASS 16; NCSS, LLC) software, and drawing effect size estimates from the literature on the impact of pharmacist counseling on diabetes control [59,60]. This analysis shows our planned sample size of 40 will provide a power of 0.85 to detect a significant change from baseline in outcome measures. Outcome measures include improvements in adherence and a reduction in HbA_1c_ and fasting glucose. We will evaluate differences before and after the intervention (eg, 3‐8 months later) using repeated-measures mixed-effects models, enabling us to evaluate not only the significance of change but also the impact of key covariates (age, gender, and health literacy) and effect size for use in planning a larger trial.

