**Methods:**

Our team previously developed a prototype computer-delivered, culturally adapted intervention targeting health literacy and adherence among older Hispanic individuals. The proposed project involves transforming this intervention into a modernized digital health app. We will achieve 2 specific aims. The first aim is to refine and modernize previously developed content into an interactive digital health app suitable for older Hispanic adults with T2D and ACC pharmacists. A total of 20 patients and 10 ACC pharmacists will review and provide feedback on the app modules. Usability and acceptability will be measured using validated tools, including the System Usability Scale, Adjectival Ease of Use Scale, and the technology acceptance model. The second aim is to conduct a pilot test with 40 Hispanic adults (aged ≥50 years) diagnosed with T2D. Participants will be recruited from a local Federally Qualified Health Center where ACC pharmacists manage diabetes care. Patients will complete a baseline CMM session, interact with the app modules, and return for 1 or 2 CMM follow-up visits. We will assess medication adherence, hemoglobin A_1c_, and fasting glucose levels as primary outcomes.

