### Evaluation Outcomes

After completion of Phase III, we will have produced 2 refined digital health apps. The Patient app will house the diabetes content for the patient to review and complete, while the Provider app will be able to transform the patients’ responses to the modules into an easy-to-read, pragmatic format to provide precision counseling. As a result, both apps will be ready for deployment and testing in a larger-scale study using a control group. The study will also provide a foundational framework for application to different diseases, languages, and cultures, and health care providers, potentially having a wider impact. This study will provide the foundation for our team to conduct a large-scale, robust, and pragmatic trial of the integration of the Patient and Provider apps into ambulatory care clinical pharmacist patient care services in geographically diverse federally qualified health centers to improve T2D medication use and outcomes. We plan to pursue such a larger-scale study, estimated to last 5 years via the R01 funding mechanism, to test the longer-term impact of the apps on health outcomes. In future studies, based on patient responses to these modules, follow-up visits, and as determined by the health care providers, we plan to implement artificial intelligence technology to deliver tailored prompts (via texts) to maintain and promote patient engagement and activation.

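### The pilot's uncontrolled before-after effect size is earmarked for planning a controlled trial and credited to the apps, but it does not estimate the between-arm difference and is likely to overstate it

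*Protocol article*

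**What the plan says.** Phase III is a single-group study. Under Procedures, Aim 2, the article says "We will evaluate differences before and after the intervention", using repeated-measures mixed-effects models at about 3 to 8 months. It lists among the products of that model an "effect size for use in planning a larger trial". Evaluation Outcomes describes what comes next: "both apps will be ready for deployment and testing in a larger-scale study using a control group", and a large pragmatic trial of the "integration of the Patient and Provider apps into ambulatory care clinical pharmacist patient care services". The comparator is not described.

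The abstract's Methods shows what each Phase III patient receives: "Patients will complete a baseline CMM session, interact with the app modules, and return for 1 or 2 CMM follow-up visits". The Introduction's section on CMM calls it a standard of care and says that some data show benefit on adherence and HbA1c, while other studies are inconclusive.

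Recruitment limits entry to patients below 80% adherence, with HbA1c above 7% and fasting glucose above 125 mg/dL. These are the same three variables that serve as outcomes.

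Aims and Hypotheses, Phase III and Results all state that the app or apps will produce the improvement from baseline, including an HbA1c reduction of at least 0.75%. Limitations says "there is no control group for the pilot study" and that attribution to the intervention may therefore be limited.

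**The concern.** A controlled trial is sized on the difference between arms. The pilot will estimate the change within one arm, which has at least four parts: what the apps add, what CMM does, what would have changed over 3 to 8 months anyway, and regression to the mean from the entry thresholds.

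Time trends and regression to the mean appear in any control arm and drop out of the comparison. The CMM part drops out as well if controls receive CMM. Regression to the mean always acts in the direction of apparent improvement here, because patients are selected on the unfavourable side of all three outcomes. Only the part that separates the arms should size the next trial, and this design cannot isolate it.

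Two things are at stake. A reader of the pilot could take the whole change as the apps' effect, as the hypothesis is worded. And anyone who entered that effect size as the between-arm difference would probably make the larger trial too small.

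**Working it through.** **1. The plan's own figure.** The article says "our planned sample size of 40 will provide a power of 0.85 to detect a significant change from baseline in outcome measures". It gives no numeric effect size, SD, alpha, sidedness or dropout, so 0.85 cannot be reproduced. It can be inverted under an assumed test. For a paired t test with n = 40, power is P(T > t_crit), where T is noncentral t with 39 df and noncentrality d × √40. Setting power to 0.85:

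| Assumed alpha | Implied d (SD-of-change units) |
|---|---|
| Two-sided 0.05 | 0.486 |
| One-sided 0.05 | 0.432 |
| Two-sided 0.05/3 (Bonferroni, three outcomes) | 0.563 |

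The article used a mixed-effects simulation, so these are approximations. A 0.75 HbA1c reduction would match d = 0.486 if the SD of change were 0.75 / 0.486 = 1.54, which the article neither gives nor contradicts.

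**2. Scaling, independent of SD.** Per-arm size for two means is proportional to 1/δ². If the apps account for a share s of the change, the true difference is s × δ and the required size is multiplied by 1/s²:

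- s = 0.75: 1/0.5625 = 1.78
- s = 0.50: 1/0.25 = 4
- s = 0.25: 1/0.0625 = 16

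The documents do not give s; the range is assumed.

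**3. In patients.** Two-sample t test, two-sided 0.05, 80% power, treating 0.486 as if it were a between-arm d:

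| Apps' share | d | Needed per arm | Power with 68 per arm |
|---|---|---|---|
| 100% | 0.486 | 68 | 0.80 |
| 75% | 0.364 | 120 | 0.56 |
| 50% | 0.243 | 267 | 0.29 |
| 25% | 0.121 | 1,065 | 0.11 |

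**4. How soft the starting point is.** One-sided alpha gives 86 per arm and Bonferroni gives 51. The 0.486 is also in units of the SD of change. In raw outcome SD units, d = 0.486 × √(2(1 − r)), where r is the pre-post correlation (assumed):

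- r = 0.3: 0.486 × √1.4 = 0.575, or 49 per arm
- r = 0.7: 0.486 × √0.6 = 0.376, or 112 per arm

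So the starting size runs from roughly 49 to 112 per arm. The multipliers in step 2 do not depend on it.

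**5. Regression to the mean alone, for HbA1c.** Expected apparent drop = (1 − ρ) × SD × λ, where ρ is the test-retest correlation and λ = φ(a)/(1 − Φ(a)) with a = (7 − μ)/SD. Assumed ranges: clinic mean μ 7.0 to 8.0, SD 1.2 to 1.6, ρ 0.7 to 0.9.

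- Smallest (μ 8.0, SD 1.2, ρ 0.9): 0.1 × 1.2 × 0.353 = 0.042
- Largest (μ 7.0, SD 1.6, ρ 0.7): 0.3 × 1.6 × 0.798 = 0.383

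Against the 0.75 target this is 0.042/0.75 = 6% to 0.383/0.75 = 51%, with no treatment effect at all.

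**The case against.** The strongest reply is that the article never says the before-after change will be entered as the between-arm difference. It says only that the effect size will help to plan a larger trial, and it names neither the comparator nor the sizing method. That stands: a reader might infer that the next trial will be undersized, but the text shows only a risk of it. The authors also see the attribution problem, since Limitations states it. That statement, however, concerns interpretation of the pilot and leaves the planned use of the effect size and the wording of the hypothesis untouched.

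Three other readings are tempting and not supported.

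- *The power calculation is wrong because it is based on counselling.* It is described as "drawing effect size estimates from the literature on the impact of pharmacist counseling on diabetes control". What is powered is total change under CMM plus apps, and counselling effects are a reasonable basis for that total.
- *Medication changes between visits are pure background care.* In Phase III and Principal Findings, the app captures a cost barrier and prompts the pharmacist to act. Such changes are partly the apps' own route of action.
- *CMM necessarily accounts for much of the change.* If patients already had CMM before enrolment, it may add little. The article recruits where pharmacists already manage diabetes care and does not say how much CMM came before.

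If the controls had no CMM, the CMM part would belong to the contrast. The description of apps integrated into existing pharmacist services suggests otherwise, without settling it. Time trends and regression to the mean would remain in either case.

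**Conclusion.** The point holds. The single-group change does not estimate the difference that a controlled trial needs. It is likely to overstate that difference, most securely through regression to the mean and, if controls receive CMM, through CMM as well. A time trend could in principle run either way.

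The secure size statement is the 1/s² scaling: about 1.8, 4 or 16 times as many patients if the apps' share is 75%, 50% or 25%. The per-arm numbers and powers are illustrations. They rest on an assumed share, an assumed paired t test at two-sided 0.05, and an SD-of-change effect used as a between-arm d. None of them is the correct size of the next trial.

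The pilot's conduct, data and within-group test are unaffected. What changes is what the pilot may claim and what it may pass on. The article's closing conclusions make no claim of app efficacy on the Aim 2 outcomes and need no change.

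**What to change.** 1. **Procedures, Aim 2.** Replace the clause on effect size for planning with wording such as: *The pilot will provide estimates of the outcome SD, the SD of change, the within-patient correlation, and the recruitment, retention and module-completion rates. The before-after change will not be used as the between-arm difference in a controlled trial; that difference will be justified separately against the chosen comparator.*
2. **Aims and Hypotheses, Phase III and Results.** State the Aim 2 hypothesis as change from baseline under CMM supported by the apps, keeping the existing targets.

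The source of the power calculation can stay as it is, and no external or chart-based comparison group is needed. The cost is a few sentences of text, with no new data and no change to procedures. Results reports that only the Phase II submission to the ethics board has been made, so Phase III has not begun. The downside is a more modest claim for the apps.
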